## Abstract

**Background:**

Parkinson’s disease (PD) is the second most common neurodegenerative disorder and seriously affects quality of life globally. Moxibustion is widely used to treat neurodegenerative diseases in the clinic and has achieved a beneficial clinical effect. However, strict control and high-quality randomized controlled trials are still lacking. Therefore, this trial aims to evaluate the clinical efficacy and safety of moxibustion in patients with PD and preliminarily explore the underlying mechanism.

**Methods:**

This is a randomized, single-blind and placebo-controlled trial design in which 70 eligible participants will be randomly divided into a moxibustion group and a sham moxibustion group. Baihui (DU20) and Sishenchong (EX-HN1) are selected for both groups. The treatment will be performed for 30 min per session, two sessions a week for 8 weeks. The mean change in MDS-UPDRS scores (including MDS-UPDRS II, III subscale scores and total scores) from baseline to the observation points will be the primary outcome. The secondary outcomes will include scores on the Parkinson’s Disease Questionnaire-39 (PDQ-39), Fatigue Severity Scale (FSS), Parkinson Disease Sleep Scale (PDSS), Montreal Cognitive Assessment (MoCA), and Self-Rating Depression Scale (SDS) as well as the Wexner constipation score. All the above outcomes will be assessed at 4 and 8 weeks. Laboratory blood biochemical analysis and functional magnetic resonance imaging (fMRI) will be conducted at baseline and at the end of treatment to explore the potential mechanisms of moxibustion in regulating PD.

**Discussion:**

In conclusion, the results of this trial will reveal whether moxibustion is effective for treating motor and nonmotor symptoms in PD. This trial will also preliminarily explore the underlying mechanism of the regulatory effect of moxibustion in PD, which will contribute to providing a theoretical basis for the treatment of PD.

**Trial registration:**

ClinicalTrials.gov ChiCTR2000029745. Registered on 9 August 2021.

## Background

Parkinson’s disease (PD) is characterized by movement slowness, tremor, rigidity, and even worse walking disorder [1]. According to the latest Global Burden of Parkinson's Disease Study, approximately 6.1 million people suffered from PD globally in 2016, and PD became the second most common neurodegenerative disorder and the fastest-growing disease that seriously affected the quality of life, resulting in 211296 deaths globally in 2016 [2]. The guidelines of PD indicate that the current first-line treatments for controlling PD symptoms mainly include medicine (levodopa, dopamine agonists, MAO-B inhibitors and COMT inhibitors) and surgery (deep brain stimulation (DBS)) [3, 4]. These treatments can effectively relieve motor symptoms for most PD patients. However, these treatments have a shortened honeymoon period and easily induce motor complications (dyskinesia, wearing-off, on and off, etc.) and other side effects that impact the use of these treatments and lead to a poor quality of life for PD patients, especially those taking high-dose and long-term antiparkinsonian drugs [5, 6]. Therefore, many researchers and patients seek complementary treatments to solve these problems. Among complementary therapies, moxibustion is a treatment that ameliorates PD symptoms and could reduce the side effects associated with the clinical use of antiparkinsonian medicine [7].

Moxibustion, a therapy that combines heat and moxa aroma radiation, focuses on acupuncture points to cure the disease [8]. Our previous studies indicated that moxibustion could reduce the motor symptoms of PD model behavior and exert a protective effect on dopamine neurons. The potential mechanism by which moxibustion regulates PD might involve enhancing the antiferroptotic defense effect of dopamine neurons [9, 10]. However, present studies mostly rely on preclinical research, and clinical trials concerning the use of moxibustion to treat PD are still lacking. From the clinical observation, moxibustion is widely used in neurodegenerative diseases such as Alzheimer's disease and PD in the clinic and has also achieved a beneficial clinical effect. However, strict control and high-quality randomized controlled trials with a low risk of bias are still needed to provide more robust evidence.

Therefore, we designed a randomized, single-blind and placebo-controlled study to evaluate the clinical efficacy and safety of moxibustion in patients with PD and to explore the underlying mechanism of the effect of moxibustion on PD by conducting blood biochemical analyses and functional magnetic resonance imaging (fMRI). The results of this study will provide more basic evidence for the clinical use of moxibustion for treating PD.

## Methods/design

### Study design

This is a randomized, single-blind and placebo-controlled trial to evaluate the efficacy and safety of moxibustion in patients with PD. Seventy patients who have been diagnoses with Parkinson’s disease will be randomly assigned to the moxibustion group or a sham moxibustion group at a 1:1 ratio. This protocol has been registered at the China Clinical Trial Registry (No. ChiCTR2000029745). The flowchart of this study design is shown in Fig. 1, and the specific schedule of screening, intervention allocation and assessments are summarized in Fig. 2.

**Fig. 1 Fig1:**
[figure not shown]
Flow chart of study design

**Fig. 2 Fig2:**
[figure not shown]
Study schedule of enrollment, intervention and assessment time points. MDS-UPDRS, MDS-Unified Parkinson’s Disease Rating Scale; PDQ39, Parkinson’s Disease Questionnaire-39; FSS, Fatigue Severity Scale; PDSS, Parkinson Disease Sleep Scale; WCS, Wexner constipation score; MoCA, Montreal Cognitive Assessment; SDS, Self-Rating Depression Scale

### Recruitment

Participants with a PD diagnosis will be recruited by doctors from the Parkinson disease clinic at the Shenzhen Hospital of Integrated Traditional Chinese and Western Medicine. Recruitment advertisements will be posted on the hospital, public places, network, and WeChat platforms to ensure that a sufficient sample size is obtained.

### Eligibility criteria

#### *Inclusion criteria*:

Participants are aged between 30 and 80 years old;Fulfilment of the diagnostic criteria for Parkinson's disease in China (2016 version) and Hoehn-Yahr (H-Y) stage < 3 [11]Participants volunteered to participate in the trial and sign the informed consent

#### *Exclusion criteria*:

Other secondary Parkinson's syndrome and Parkinson's superimposed syndromePatients with dementia and mental disorders who are unable to communicate and cooperate;Participants who have a history of severe cerebrovascular or brain trauma or brain surgery;Complications with severe heart, lung, liver, kidney and other systemic organic diseases, endocrine diseases and metabolic disorders;Participants who allergies to moxibustion treatment;Participants who have undergone DBS surgery;Patients who are participating in other clinical trials;Other reasons that make a patient not suitable for the clinical trial as judged by the clinicians.

### Randomization and allocation concealment

In this trial, random numbers will be generated using SPSS by a researcher coordinator who is not in contact with the participants. Then, the random numbers will be sealed in sequentially numbered, opaque envelopes and delivered to clinicians. Another clinician in the clinic center will assign the patients who meet the inclusion criteria and sign the informed consent to the moxibustion or sham moxibustion groups based on the contents of the envelopes.

### Blinding

Practitioners could not be blinded because of the unique characteristics of moxibustion intervention. However, the participants will be blinded to the moxibustion and sham moxibustion group allocation. The participants will be allocated to the individual isolated treatment rooms, avoiding communication with each other. To ensure the reliability of the results, outcome assessors, personnel responsible for data collection and data statistics will be blinded to the group information and specific allocation in the entire trial.

### Intervention

The basic medicine treatment of PD in this trial will follow the principles of clinical guidelines and will not be strictly standardized because of the complexity and individualized clinical manifestations of PD. However, the dosage of the medicine taken will be recorded and cannot be changed casually.

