### Outcome measures

The mean change in MDS-UPDRS scores (including MDS-UPDRS II, part III subscale, total score) from baseline to the observation points will be the primary outcomes. Scores on the Parkinson’s Disease Questionnaire-39 (PDQ-39), Fatigue Severity Scale (FSS), Parkinson Disease Sleep Scale (PDSS), Montreal Cognitive Assessment (MoCA), and Self-Rating Depression Scale (SDS) as well as the Wexner constipation score will be regarded as secondary outcomes and will be assessed at 4 and 8 weeks. All initial assessments will be followed up at week 16.

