### Statistical analysis

Statistical analysis of the data will be conducted by researchers blinded to group assignments using SPSS (version 25). Intention-to-treat analysis will be performed for all assigned participants. The missing data will be imputed by the last observation carried forward (LOCF) method. All included data will be first tested to determine whether they meet the normality test. If data conformed to a normal distribution, the mean ± standard deviation will be used. Otherwise, data will be expressed as M (P25-P75). An unpaired t test will be used when the data meet a normal distribution; otherwise, a nonparametric test (Mann–Whitney U) will be used to analyze comparisons between the moxibustion group and the control group. A P value less than 0.05 will be considered statistically significant.

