## Discussion

The treatment of Parkinson’s disease has attracted increased attention from doctors and researchers in recent years. Although dopaminergic drug therapy is effective for controlling motor symptoms, side effects and motor complications are often induced by taking these medicines [13, 14]. Therefore, combining alternative therapies may be helpful to solve these problems. Moxibustion, as a traditional Chinese medical therapy, is beneficial for ameliorating motor and nonmotor symptoms to some extent based on clinical observations. However, high-quality trials and evidence concerning the efficacy of moxibustion for treating PD are still lacking. The objective of this trial is to confirm the effectiveness and safety of moxibustion in patients with PD and provide evidence for physicians to better improve clinical effectiveness in treating PD.

In this study, we selected the early stage of PD as our research objective because our previous preclinical studies indicated that moxibustion was effective for reducing the death of dopaminergic neurons and improving motor behavior in the early stage of PD [9, 10]. From the point of view of the clinic, the earlier the moxibustion intervention is implemented, the better the effect will be. The later stage of PD is always accompanied by severe damage and loss of dopamine neurons, and any intervention in this stage will be hard to remedy and attain satisfactory symptomatic control [15]. Therefore, to obtain a better clinical effect and observe significant group differences, we only included patients with early-stage PD.

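### PD medication may vary and change, but the MDS-UPDRS ratings are tied to no medication state and the stated test ignores the recorded dose: mainly lost precision, with bias only if dose changes differ by arm

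*Protocol article*

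**What the plan says.** **Medication.** Under Intervention, the protocol article says that basic PD medicine follows clinical guidelines but "will not be strictly standardized because of the complexity and individualized clinical manifestations of PD". It adds that "the dosage of the medicine taken will be recorded and cannot be changed casually". It does not say what counts as a casual change, and the eligibility criteria set no stable-dose condition at entry.

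**Outcome.** Under Outcome measures, the primary outcome is "The mean change in MDS-UPDRS scores (including MDS-UPDRS II, part III subscale, total score) from baseline to the observation points". No on or off state and no time since the last dose is attached to these ratings in the text shown.

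**Analysis.** Under Statistical analysis, the comparison follows intention to treat, with last observation carried forward. The first choice of test is given as "An unpaired t test will be used when the data meet a normal distribution". Where the normality check fails, the plan switches to the Mann–Whitney U test. No covariate is named, and the recorded dose has no stated use.

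**The authors' own account of the drugs.** The Discussion says that "dopaminergic drug therapy is effective for controlling motor symptoms". The Background says that current treatments "easily induce motor complications (dyskinesia, wearing-off, on and off, etc".

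**The concern.** By the article's own account, dopaminergic drugs act on what the primary outcome measures, and their effect can wear off between doses. The plan lets this influence vary between patients and over time and collects data on it. It then fixes an analysis that leaves the data unused. Two separate things are at stake.

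- **Precision.** If a patient is rated soon after a dose at one visit and long after a dose at another, the change score carries a medication component unrelated to moxibustion. Different regimens also add between-patient spread and, in a trial of 70, some chance imbalance.
- **Bias.** If doses are raised more often in the arm that is doing worse, that arm's scores absorb the drug benefit and the moxibustion contrast shrinks.

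**Working it through.** **1. The plan's own figure.** The Sample size section uses effective rates of 0.933 and 0.633, deviates 1.96 and 0.842, and 15% dropout.
- Pooled p = (0.933 + 0.633)/2 = 0.783.
- n = 2 × (1.96 + 0.842)² × 0.783 × 0.217 / 0.30² = 29.64 per group.
- 29.64 / 0.85 = 34.88, rounded up to the stated 35.

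The figure reproduces and is not in dispute. It rests on responder rates, so it contains no MDS-UPDRS variance and no allowance for medication state.

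**2. Precision (illustration).** Assumptions, none of them from the documents: SD of part III change 8 points; independent state-related SD of s points at each of two visits, added on top. The number evaluable is 35 × 0.85 ≈ 30 per arm; two-sided alpha is 0.05.
- The effect detectable with 80% power by a t test is 0.736 SD, or 0.736 × 8 ≈ 5.9 points.
- Variance of change = 8² + 2s² = 64 + 2s².

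| s (points) | Variance | Standardised effect, 0.736 × √(64/variance) | Power |
|---|---|---|---|
| 0 | 64 | 0.736 | 80% |
| 1 | 66 | 0.724 | 79% |
| 2 | 72 | 0.694 | 75% |
| 4 | 96 | 0.601 | 63% |

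The same point without fixing an SD: extra variance of 10%, 25%, 50% or 100% in both arms takes power (normal approximation, detectable effect 0.72 SD) from 80% to 76%, 71%, 63% or 51%.

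**3. Bias (illustration).** Assume that 20% of sham patients and no moxibustion patients have a dose increase worth 5 points. The contrast shrinks by 0.20 × 5 = 1.0 point, which is 1.0/5.9 ≈ 17% of the detectable difference above. If the same share in each arm gains the same amount, the shift cancels and nothing is left but noise.

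**4. Which mechanism the design leaves open.**
- *Baseline regimen:* balanced in expectation by 1:1 randomisation. A constant regimen also largely drops out of a change score.
- *State at rating:* assessors and participants are blinded, so the text gives no route for it to differ by arm. It adds noise.
- *Dose changes after randomisation:* not excluded. They can differ by arm if one arm does worse, even when nobody knows the allocation. In addition, "Practitioners could not be blinded because of the unique characteristics of moxibustion intervention".

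**The case against.** **Much of this is detail left to other documents.** Medication state at rating, dose tables and covariates often sit in a full protocol or SAP, and the schedule figure is not shown. That is fair, and their absence alone is no finding. What stands is what the article does fix: an undefined limit on change, a drug-sensitive primary outcome with no state in the text, and a named unadjusted test that can be improved with data already collected.

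**A reader might infer that drug effect is certainly mixed into the primary contrast.** The documents do not support this. Randomisation, change-from-baseline scoring and blinded assessment leave mainly noise; bias needs dose changes that differ by arm, and nothing shows that they will.

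**A reader might also infer a raised false-positive rate.** That would need an arm difference in dosing when moxibustion does nothing. Dose increases in the arm doing worse create no such difference when the arms do equally well, and otherwise they act toward no difference.

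**Under intention to treat, later medication changes may be part of the strategies compared.** This stands. The treatment-policy comparison is legitimate and should stay primary; the unchanged-medication question belongs in a sensitivity analysis.

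**The fluctuation argument may not fit these patients.** The Background links motor complications especially to high-dose, long-term drug use, whereas the trial enrols Hoehn-Yahr stage below 3, which the Discussion calls early-stage. This stands as a reason to expect the smaller values of s.

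**The numbers are assumed and may double count.** This also stands. An SD of change from ordinary practice would already include some state variation, so adding 2s² overstates the loss. At s = 1 the loss is only about one percentage point.

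**Conclusion.** The point holds as a matter of precision and of a possible, conditional bias. Medication is unstandardised and may change, the primary ratings are tied to no medication state in the text shown, and the stated test does not use the recorded dose. The likely consequence is noise and chance imbalance in a small trial. Attenuation of the moxibustion effect follows only if dose changes differ by arm.

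The size cannot be set from the documents, which give no MDS-UPDRS SD and no drug effect. The illustration of 80% power falling to about 75% or 63% rests on an assumed SD of 8, 30 evaluable per arm and 2 or 4 points of added SD per visit, and it overstates the loss if the 8 already includes state variation. The change is worth making because it is cheap and can be made without altering the design. The point does not show that the planned comparison is invalid.

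**What to change.** 1. **Measurement.** Rate each patient's MDS-UPDRS in the same medication state, and at a similar interval after the usual dose, as at that patient's baseline. Record the time of the last dose and of the rating.
2. **Primary model.** Replace the unadjusted test with ANCOVA on the week-8 score, adjusted for baseline score and baseline levodopa-equivalent dose. Do not adjust for dose after randomisation, because treatment may affect it. The baseline dose covariate deals with chance imbalance and spread, not with later changes.
3. **Dose changes.** Keep the intention-to-treat (treatment-policy) comparison as primary and tabulate medication changes by arm. Add one prespecified sensitivity analysis that sets scores after a medication change to missing and multiply imputes them, rather than carrying the last value forward. State before unblinding what counts as a change for this analysis.

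The cost is one time field on the CRF, some constraint on visit scheduling, the conversion of recorded doses to levodopa equivalents, and a little more analysis. The sensitivity analysis assumes that the removed scores are missing at random given the data in the imputation model, which should be stated. No rule on medication itself is proposed.

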#### Treatment group

Participants in each group will receive moxibustion and sham moxibustion intervention on Baihui (DU20) and Sishenchong (EX-HN1). In true moxibustion therapy, a moxa stick is ignited at the tip and positioned with a moxibustion supporting apparatus, and the burning tip of the moxa stick is positioned 3 cm above the corresponding acupoints. The intolerable and comfortable temperature without any burning pain above the acupoints will be controlled at 40-43 °C by a temperature thermometer. The treatment will last for 30 min per session, two sessions a week for 8 weeks (16 times). Follow-up will be conducted at week 16.

#### Control group

In the control group, participants will receive sham moxibustion treatment at the same acupoints as the true moxibustion treatment used. The nonmoxa floss stick will be ignited and positioned 8-10 cm above the acupoints. However, the temperature above the acupoints will be maintained at 37 °C, and patients will not receive any warm therapy at the acupoints. The treatment procedure and treatment duration of the sham moxibustion group will follow those of the treatment group.

### Outcome measures

The mean change in MDS-UPDRS scores (including MDS-UPDRS II, part III subscale, total score) from baseline to the observation points will be the primary outcomes. Scores on the Parkinson’s Disease Questionnaire-39 (PDQ-39), Fatigue Severity Scale (FSS), Parkinson Disease Sleep Scale (PDSS), Montreal Cognitive Assessment (MoCA), and Self-Rating Depression Scale (SDS) as well as the Wexner constipation score will be regarded as secondary outcomes and will be assessed at 4 and 8 weeks. All initial assessments will be followed up at week 16.

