### Sample size calculation

A previous study explored relevant moxibustion plus basic medicine treatment versus placebo plus basic medicine treatment for PD. We extracted effective rates of 93.3% in the moxibustion group (p1) and 63.3% in the placebo group (p2) [12]. Based on these values, we calculated the sample size using the following formula: *n* = 2(u_a_ + u_b_)^2^_*_p(1-p)/(p_1_-p_2_)^2^, *p* = (p_1_*n_1_ + p_2_*n_2_)/(n_1_ + n_2_). The significance level is 0.05, and the probability values of the first type of error (u_a_) and second type of error (u_b_) are 1.96 and 0.842, respectively. The dropout rate is 15%. The estimation indicated that 35 patients were required for each group, and the total sample size was 70 patients.

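### Three overlapping MDS-UPDRS scores at two or three visits are all primary, each judged at an unadjusted 0.05, with no decisive score, visit or success rule

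*Protocol article*

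**What the plan says.** The Abstract (Methods) describes the change in MDS-UPDRS scores as "including MDS-UPDRS II, III subscale scores and total scores) from baseline to the observation points will be the primary outcome". The Outcome measures section names the same three scores but uses the plural: "including MDS-UPDRS II, part III subscale, total score) from baseline to the observation points will be the primary outcomes". Neither place says which observation point is meant.

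The timing has to be pieced together. The Abstract says "All the above outcomes will be assessed at 4 and 8 weeks". The Outcome measures section adds "All initial assessments will be followed up at week 16", and the Treatment group section says "Follow-up will be conducted at week 16".

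For the between-group comparison, the Statistical analysis section says "An unpaired t test will be used when the data meet a normal distribution", with Mann-Whitney U otherwise. It then gives a single criterion: "A P value less than 0.05 will be considered statistically significant". The Sample size calculation section uses one comparison: "The significance level is 0.05".

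**The concern.** A primary outcome should fix in advance the one result, or the stated combination of results, on which the trial's conclusion rests. Here the article leaves open which score counts, which visit counts, and whether one significant result is enough or all are needed. The sponsor could pick among 6 to 9 results after seeing them and still be following the text.

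The article says the trial will answer whether moxibustion is effective. If a single significant result out of the set is used to support that answer, the error rate behind it is not the 5% that the threshold suggests.

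**Working it through.** **Inputs from the article**
- Scores: part II, part III, total (Abstract; Outcome measures).
- Visits: weeks 4 and 8 (Abstract); week 16 as follow-up (Outcome measures; Treatment group).
- Threshold: 0.05 per test, no adjustment stated (Statistical analysis).
- Sample size: u_a = 1.96, u_b = 0.842, rates 93.3% and 63.3%, dropout 15% (Sample size calculation).

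**Step 1. The plan's own figure.** Pooled p = (0.933 + 0.633)/2 = 0.783.

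n = 2 × (1.96 + 0.842)² × 0.783 × 0.217 / 0.30² = 29.64

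29.64/0.85 = 34.88, so 35 per group. The stated 35 per group and 70 in total reproduce. The calculation covers one comparison at two-sided 0.05 and makes no allowance for several tests.

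**Step 2. Number of primary tests.** 3 scores × 2 visits = 6; 3 scores × 3 visits = 9.

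**Step 3. Reference values if the tests were independent.**
- 6 tests: 1 − 0.95⁶ = 26.5%
- 9 tests: 1 − 0.95⁹ = 37.0%

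The scores overlap and the visits share patients, so the true values lie below these.

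**Step 4. Correlated tests, no treatment effect.** The article gives no correlations, so these are assumptions. The three score sets (II–III, II–total, III–total) were (0.3, 0.6, 0.85), (0.5, 0.75, 0.9) and (0.6, 0.8, 0.92). The correlation of changes between visits was 0.4, 0.6 or 0.8. Simulated ranges across these scenarios:

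| | 6 tests | 9 tests | one test |
|---|---|---|---|
| At least one two-sided P < 0.05 | 14-20% | 18-28% | 5% |
| At least one P < 0.05 favouring moxibustion | 7-10% | 9-14% | 2.5% |

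Both rows show roughly a three- to six-fold inflation. Three scores at a single visit already give about 10-11% two-sided.

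**Step 5. Sensitivity to the correlation model.** A second model built the total as the sum of four parts (assumed SDs 3, 4, 8 and 1.5), with between-part correlation 0 to 0.7 and between-visit correlation 0 to 0.9. It gave 12-22% for 6 tests and 14-31% for 9. A correlation of 0.9 between all tests gave about 11% and 12%. Even there the rate is about twice nominal.

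**Step 6. Cost of adjusting instead of choosing.** The Bonferroni threshold is 0.05/6 = 0.0083 or 0.05/9 = 0.0056. For nine tests, 80% power and 35 per arm (all assigned patients analysed, with last observation carried forward), the detectable difference rises from 0.68 to 0.89 SD. On 30 completers per arm it rises from 0.74 to 0.97 SD. Bonferroni is the most costly adjustment for tests this correlated; naming one primary costs nothing in detectable effect.

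**The case against.** **An analysis plan that is not shown may handle multiplicity.** It may add an adjustment. But choosing the primary outcome belongs to the protocol, and this text has chosen: three scores, unnamed visits, one flat threshold. The point concerns what is fixed, not what is left out.

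**The text does not say that one significant result is enough.** This stands. The article defines when a P value is significant, not when the trial has succeeded. If all primary tests had to be significant, the error would be at most 5%. The percentages are therefore conditional on the any-one reading. The absence of a rule is not conditional.

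**Week 16 may be only a durability follow-up.** This also stands, and it is at least as natural a reading. Under it there are 6 tests, and the two-sided figure under the Step 4 assumptions stops at about 20%.

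Three stronger readings are tempting but not supported:
- A reader might take 14-28% as the chance of wrongly declaring moxibustion effective. Those figures also count results in which sham looks better. In the favourable direction the figures are about half, against a nominal 2.5%.
- A reader might infer that requiring all tests to succeed would pull power below the planned 80%. That 80% was calculated for a binary effective rate, so it is not a baseline for the MDS-UPDRS change scores.
- A reader might infer that part III is the only proper choice. The Blinding section applies blinding to all outcome assessors, so assessor blinding does not single out part III. The choice is the sponsor's.

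**Conclusion.** The concern holds. The primary outcome is not pinned to one score, one visit or a success rule, and as written the plan does not hold the primary error at 5%.

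The size of the inflation rests on three things the article does not settle: that any one significant result counts as success, the assumed correlations, and, for the nine-test figures, that week 16 is a primary visit. Other correlation assumptions shift the percentages, but no scenario examined under the any-one reading comes near the nominal level. The main reason to correct the text is the undefined primary outcome; the percentages show what it can cost.

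**What to change.** Before unblinding:

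1. Name one primary outcome: one MDS-UPDRS score at one visit, tested at two-sided 0.05. Part III at week 8, the end of treatment, is one example; the sponsor should choose.
2. Make the other two scores at that visit key secondary outcomes, tested in a fixed sequence after the primary or with Holm's procedure.
3. Report the other visits, week 16 included, and the other scales as supportive estimates with confidence intervals and no significance claim.
4. Use the same wording in the Abstract, the Outcome measures section and the Statistical analysis section, and update the registry entry.

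The cost is wording and a registry update, with no change in sample size, visits or data collected. The Trial status section reports recruitment as still under way when the article was written. The downside is fewer outcomes that can be claimed as primary successes.
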